## Abstract

**Background:**

Myanmar has a high burden of mortality for children aged younger than 5 years in which undernutrition plays a major role. Despite current efforts, the exclusive breastfeeding rate for children under 6 months is only 24%. To date there have been no interventions using mobile phones to improve breastfeeding and other feeding practices in Myanmar.

**Objective:**

This study aims to implement a breastfeeding promotion intervention using mobile phone text messages in Yangon, Myanmar, and evaluate its impact on breastfeeding practices.

**Methods:**

M528 is a 2-group parallel-arm randomized controlled trial with 9 months follow-up from recruitment until 6 months post-delivery. A total of 353 pregnant women between 28 and 34 weeks’ gestation who had access to a mobile phone and were able to read and write have been recruited from the Central Women’s Hospital, Yangon, and allocated randomly to an intervention or control group in a 1:1 ratio. The intervention group received breastfeeding promotional SMS messages 3 times a week while the control group received maternal and child health care messages (excluding breastfeeding-related messages) once a week. The SMS messages were tailored for the women’s stage of gestation or the child’s age. A formative qualitative study was conducted prior to the trial to inform the study design and text message content. We hypothesize that the exclusive breastfeeding rate in the intervention group will be double that in the control group. The primary outcome is exclusive breastfeeding from birth to 6 months and secondary outcomes are median durations of exclusive breastfeeding and other infant feeding practices. Both primary and secondary outcomes were assessed by monthly phone calls at 1 to 6 months postdelivery in both groups. Participants’ delivery status was tracked through text messages, phone calls, and hospital records, and delivery characteristics were assessed 1 month after delivery. Child morbidity and breastfeeding self-efficacy scores were assessed at 1, 3, and 5 months postdelivery. Social desirability was measured at 5 months, and text messages expressing delivery success and user experience were assessed at the end of the study.

**Results:**

The targeted 353 pregnant women were recruited between January and March 2015. Baseline data have been collected; SMS messages have been developed and pretested and sent to the women from both groups. Follow-up data collection via phone calls has been completed. Data analysis is being done and results are expected soon. This is the first RCT study examining the effects of mobile text messaging for promoting exclusive breastfeeding.

**Conclusions:**

This trial is timely in Myanmar following the telecommunications market opening in 2014. Our results will help determine whether text messaging is an effective and feasible method for promoting appropriate feeding practices and will inform further research to assess how this model could be replicated in the broader community.

**Trial Registration:**

Australian New Zealand Clinical Trial Registry ACTRN12615000063516; https://anzctr.org.au/Trial/Registration/TrialReview.aspx?id=367704 (Archived by WebCite at http://www.webcitation.org/ 6rGif3l81)

## Introduction

Globally, undernutrition is the underlying cause of an estimated 45% of deaths in young children and contributes to 35% of the disease burden in children under 5 years and 11% of total global disability-adjusted life years [1-3]. Myanmar is facing undernutrition as a public health problem, with 23% of children under 5 years of age being underweight and 35% stunted [4], which exceeds the global average of 25% [5]. Myanmar also has a high under-5 child mortality rate of 46 deaths per 1000 live births [4]. The Global Strategy for Infant and Young Child Feeding recommends that newborns should start breastfeeding within 1 hour after birth and that infants should be exclusively breastfed for the first 6 months and for an additional 18 months or longer with appropriate complementary food [6]. The benefits of breastfeeding are well documented, and breastfeeding promotion programs are a cost-effective public health measure to prevent the leading causes of child mortality such as diarrhea, pneumonia, and neonatal sepsis [7-11]. The 2013 Lancet series on maternal and child nutrition and a study in Nepal highlighted that high coverage of community-based early breastfeeding initiation and exclusive breastfeeding (EBF) promotion programs could prevent an estimated 13% of under-5 deaths and almost 20% of neonatal deaths [12-14].

In Myanmar, regardless of race or religion, breastmilk is considered the most beneficial food for newborns, and breastfeeding is culturally and socially supported in both urban and rural areas [15]. Our recent formative qualitative study showed that expectant mothers traditionally believe the benefits of breastmilk and husbands and family members support breastfeeding. However, if women have insufficient milk or have to return to work, formula milk was favored by those who could afford it due to the stereotype of affordability or influence of advertising, while poor women would provide cow or goat’s milk and sweetened condensed milk mixed with warm water or milk powder [16]. The latest national survey conducted in Myanmar reported that 90% of mothers were aware of the benefits of breastmilk and 76% fed breastmilk to their newborn within 1 hour after birth, but only 24% of infants less than 6 months of age were exclusively breastfed [4]. This EBF rate is the second lowest in the World Health Organization (WHO) South-East Asia Region after Thailand [17].

Globally, with increased availability of mobile phones, the use of mobile technology for health-related interventions (mHealth) has greatly increased [18,19]. Several maternal and child health nutrition promotional studies have used mobile text messages to disseminate educational information to a target audience. A Text4baby study in the United States reported that exposure to short message service (SMS) or text messages was associated with belief changes in pregnant women [20], and a recent meta-analysis of mHealth interventions for maternal, newborn, and child health in low- and middle-income countries found high levels of impact for EBF [21]. An Australian study conducted with 234 mothers showed that women who received breastfeeding promotional text messages had a slower decrease in EBF (6% per month) compared to the women receiving usual care, who had a 14% decrease in EBF per month (*P*<.001) [22]. Other studies also report that using mobile phones and text messaging is feasible and has promising results in smoking cessation [23,24], diabetes education [25,26], sexual health, diet [26], and physical activity [27,28].

The mobile network in Myanmar used to be solely controlled by the government and, until recently, there was low access to mobile services by the general population. Consequently, there have been no interventions in Myanmar using mobile phones to promote community health and well-being. With political reform in 2011, Myanmar is on the verge of a communications revolution. Mobile phone prices have reduced considerably and the penetration of mobile services has increased from 2% in 2011 to 49% in 2014 [29,30]. Improved mobile phone services have enabled us to plan a randomized controlled trial (RCT) using mobile phones to promote EBF practices. This planned trial is called M528 where M stands for the mobile phone and 528 is a special number in Myanmar that refers to selfless love and other emotions and represents the bonding between mother and baby.

The objective of this study is to implement a mobile phone–based EBF promotion in pregnant women attending the antenatal clinic at Central Women’s Hospital, Yangon, and to evaluate its impact on breastfeeding practices. The primary hypothesis is to test whether breastfeeding promotional text messages can help increase EBF practices in the intervention group. We hypothesize that EBF rates in the intervention group during the 6 months after delivery will be double (30%) that of the control group (15%). Although the Myanmar Multiple Indicator Cluster Survey 2010 reported that 24% of infants younger than 6 months were exclusively breastfed, only 15% of infants were exclusively breastfed until they were 6 months old [4]. We, therefore, set the control group’s EBF rate at 15% and expect that the intervention group will have EBF rate at 30% at the end of the study. This is realistic as other intervention studies using text messages to promote EBF practices have reported a more than 2-fold increase in the odds of EBF. For example, a trial in China found a higher EBF rate at 6 months postdelivery in the intervention group (adjusted odd ratios [AOR] 2.58, 95% CI 1.4-3.7) [31] and a trial in Nigeria showed a similar result (AOR 2.40, 95% CI 1.4-4.0) [32]. Our secondary hypotheses are that receiving breastfeeding promotional text messages will result in higher appropriate infant feeding practices in the intervention group compared to that of the control group. We assessed women’s feeding practices, breastfeeding self-efficacy scales, and delivery and child morbidity characteristics during follow-up. We also conducted a process evaluation at the end of the study. Our findings will also help to provide recommendations on how mHealth-based breastfeeding promotion programs can be further improved for use in wider populations.

## Methods

### Study Design

A 2-group parallel arm RCT with hospital-based recruitment and 9 months of follow-up was conducted to test the effect of a text message–based intervention for EBF promotion in participants recruited from the Central Women’s Hospital, Yangon. A total of 353 women were recruited for the study. The intervention group received breastfeeding promotional messages and the control group received pregnancy- and childcare-related messages (except breastfeeding messages) from the time of recruitment until 6 months postdelivery. The study involved conducting a formative (qualitative) study to inform the trial design and to develop text messages, recruiting pregnant women, implementing the intervention, collecting data at baseline and from 1 to 6 months postdelivery by monthly phone calls, and evaluating effectiveness at the end of the study. Figure 1 summarizes the study design of the M528 RCT using the Consolidated Standards of Reporting Trials (CONSORT) template.

**Figure 1 figure1:**
[figure not shown]
M528 trial flow diagram (as per Consolidated Standards for Reporting Trials guideline).

We used the Health Belief Model [33] that suggests that a set of beliefs, specifically beliefs about susceptibility, severity, barriers, and benefits, leads to a particular behavior. We postulate that a woman will EBF (a particular behavior) if she believes (perceived benefits) that breastmilk has all the nutrients needed for her baby for 6 months, prevents infection, and is good for the child’s physical and neurological development. She will stop giving water and formula milk while her child is under 6 months of age if she believes that these could cause diarrhea and indigestion (perceived threat: a combination of perceived severity and perceived susceptibility). She will have higher perceived self-efficacy if she receives information on how to overcome barriers (perceived barriers) such as how to manage her family’s influences, solve breast problems, and express breastmilk when returning to work. The Health Belief Model adapted for our study is described in Figure 2; an illustration showing how the text messages relate to the Health Belief Model is described in Textbox 2 (after stage 1: preparatory phase).

**Figure 2 figure2:**
[figure not shown]
Model used in M528 trial—adapted from Health Belief Model.

### Ethics Approval and Consent to Participate

The study has been approved by the Myanmar Ethical Review Committee, Department of Medical Research, Ministry of Health and Sports, Myanmar (approval number 7/ethic 2014) and the Department of Health, Ministry of Health and Sports, Myanmar (medical care-2/A-24/2014-659). The Ethical Review Committee, University of Sydney, acknowledged and approved the study based on the approval of the ethics committee in Myanmar. Furthermore, the M528 study trial is registered through Australian New Zealand Clinical Trials Registry [ACTRN12615000063516].

### Setting

The Central Women’s Hospital, Yangon, was purposely selected as it is the largest tertiary public women’s hospital in Myanmar. The antenatal care clinic operates Monday through Friday and, in 2013, the hospital reported that, on average, 2000 pregnant women visited the clinic each month. The main reason for visits is to have the opportunity to deliver at the hospital free of charge because the majority of mothers attending could not afford private hospitals or clinics. In this setting, there is a higher possibility of recruiting women from a diverse range of socioeconomic backgrounds. The hospital is accredited as a baby friendly hospital initiative and follows guidelines to provide early initiation of breastfeeding. The hospital has a policy to encourage mothers to give colostrum to babies within 1 hour after birth regardless of the type of delivery.

### Study Population

Inclusion criteria were women from 28 to 34 weeks gestation who could access a mobile phone (Android or Java) that could display Myanmar language fonts, who had an uncomplicated singleton pregnancy, who were able to read and write in the Myanmar language, and who lived in an area with mobile network coverage. Exclusion criteria were pregnancy complications, a multiple pregnancy, and known medical conditions including mental illness that might hinder breastfeeding.

### Recruitment, Assignment, and Allocation

Participant eligibility was assessed via a hospital attendance registry (used by hospital staff) and antenatal care records (kept by the participant) in which information such as age, weeks of gestation, address, and phone numbers were recorded. At recruitment, researchers identified potential participants with the help of hospital nurses, explained the study, provided an information statement and consent form written in Burmese, and confirmed eligibility. If a woman agreed to participate, informed consent was obtained, and she was requested to complete the baseline survey questions. The participant’s mobile phone was checked for compatibility with text messages and, if needed, brief training on how to read and send text messages was provided. The recruitment process took 6 weeks (January to February 2015). Out of a total of 450 potentially eligible pregnant women, 353 were confirmed to be eligible and consented to participate in the trial. Each woman received 500 Myanmar kyats (US $0.50) to compensate for sending a text message to inform the research team of her delivery date.

Eligible women were randomized to the intervention or control group according to an allocation sequence generated by a computer program [34] with a block size of 16 to ensure a balanced group size. Each study and group number was kept in an opaque envelope to conceal the allocation sequence and securely stored. At recruitment, research team members sequentially took an envelope for each consenting participant and conducted the baseline interview. After the participant’s information was recorded, the envelope was opened and the group allocation was recorded.

### Blinding

Because the intervention could not be blinded, we minimized bias by ensuring both groups received messages and by not explaining in the consent and information sheets how the text messages differed between groups. The information statement provided only general information that each participant could be allocated randomly into a group; would receive messages containing information on pregnancy, childcare, and breastfeeding practices; and that the frequency of messages could vary from 1 to 3 times per week. Research staff and interviewers (via telephone) were blinded to each participant’s group status although they might guess the group based on participants’ responses. To minimize bias, we also blinded research staff to the trial aims and hypotheses.

### Sample Size Determination

Stata version 13.0 (StataCorp LLC) was used for sample size estimation and data analysis. Sample size was calculated with the assumptions of 80% power, 5% 2-sided alpha, and 13% expected loss at follow-up. The EBF rate of Myanmar children at 6 months of age was 15% [4], and we hypothesize that EBF in the intervention group will be increased 2-fold. The estimated sample size was 312 (156 per group) and the final sample size requirement was 353 participants to allow for 13% loss at follow-up.

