### Data Analysis

Quantitative data were collected via tablets and automatically submitted to the Dimagi server from which we could monitor data and generate reports. Stata software version 13 (StataCorp LLC) was used for data analyses. The intervention and control group outcomes will be compared using intention-to-treat principles [61]. Descriptive analyses were used to summarize participant baseline characteristics and breastfeeding practices. Likert scales were analyzed using Mann-Whitney U tests or cumulative odds ratios and proportions between groups using chi-square tests. Duration of EBF was compared by survival analyses with log-rank tests for between-group comparisons. If differences in baseline characteristics of the groups are identified, multivariable analyses will be undertaken. We report results using the CONSORT guidelines for reporting of randomized trials [62]. As follow-up data collection had to rely on the mothers’ self-reporting alone, we adjusted the potential social desirability bias [43] in our analyses to confirm the accuracy of self-reported outcome measures.

For process evaluation, we used Stata software for survey data analysis. We conducted descriptive analyses to summarize participant baseline characteristics and their experiences and feedback about receiving text messages. Text message delivery success was measured by the frequencies of messages received, and proportions were compared with chi-square tests. For the qualitative study, we used thematic analysis. All digitally recorded interviews were transcribed verbatim in Burmese in Microsoft Word and were reviewed to check for accuracy and translated to English. A list of thematic codes was developed by MPH, which was independently reviewed and verified by AA. The data were then be manually coded by MPH for emerging themes, which were again verified by other investigators and the most relevant themes are summarized in a document.

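### The stated power, rates and sample size do not agree: 15% versus 30% at 80% power needs 121 to 134 women per group, not 156

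*Protocol article*

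**What the plan says.** Under Sample Size Determination the Protocol article states: "Sample size was calculated with the assumptions of 80% power, 5% 2-sided alpha, and 13% expected loss at follow-up". The control rate is 15%, and the intervention is expected to raise it 2-fold. The result follows: "The estimated sample size was 312 (156 per group"), with 353 as the requirement after allowing for loss.

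The Introduction puts the doubling on the rate scale. The rate in the intervention group "will be double (30%) that of the control group (15"%), and the authors "expect that the intervention group will have EBF rate at 30% at the end of the study".

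The Abstract says that women were "allocated randomly to an intervention or control group in a 1:1 ratio". Data Analysis says that the plan compares "proportions between groups using chi-square tests". The article mentions no design effect, split of alpha or other factor that would enlarge the sample.

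**The concern.** The article gives every input that a two-proportion sample size needs, and it gives the output. The output does not follow from the inputs. The gap of 22 to 35 women per group is too large for rounding. The 13% loss does not explain it as written, because 312 is presented as the number before loss and 353 as the number after it.

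Readers use this paragraph to judge how sensitive the trial was to its hypothesised effect, above all if the observed difference is smaller than a doubling. As written, they would credit the trial with 80% power for 15% versus 30%, when the stated numbers imply more. Anyone who reuses the calculation would copy the inconsistency.

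**Working it through.** **Inputs.** From Sample Size Determination: power 80%, two-sided alpha 5%, control rate p1 = 0.15, loss 13%. From the Introduction: intervention rate p2 = 0.30. From the Abstract: 1:1 allocation. From Data Analysis: chi-square test. Hence the difference d = 0.15 and the mean rate is 0.225.

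**1. The plan's own steps.** 2 × 156 = 312, and 312 × 1.13 = 352.6, which rounds up to 353. This confirms that 312 is the figure before loss. (Dividing instead, 312 / 0.87 = 358.6, would give 359. That does not bear on where 312 comes from.)

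**2. Sample size from the stated inputs, without continuity correction.**

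n = [1.96 × √(2 × 0.225 × 0.775) + 0.8416 × √(0.15 × 0.85 + 0.30 × 0.70)]² / 0.15²

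= [1.96 × 0.5906 + 0.8416 × 0.5809]² / 0.0225

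= [1.1575 + 0.4889]² / 0.0225 = 2.7106 / 0.0225 = 120.5, so **121 per group, 242 in total**.

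**3. With continuity correction.**

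n_c = (n / 4) × [1 + √(1 + 4 / (n × d))]², with n = 120.5 and d = 0.15, gives 133.5, so **134 per group, 268 in total**.

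**4. Other readings of the same inputs.**

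| Variant | Per group |
|---|---|
| Unpooled variance | 118 |
| Arcsine | 119 |
| Fisher's exact test | about 132 |
| One-sided alpha, without / with correction | 95 / 108 |
| Doubled odds (15% v 26.1%), without / with correction | 208 / 225 |
| **Stated** | **156** |

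None comes near 156. The stated 312 exceeds 268 by 44 women (16%) and 242 by 70 women (29%).

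**5. Power that 156 per group gives for 15% versus 30%.**

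Uncorrected: z = (0.15 × √156 − 1.1575) / 0.5809 = 1.23, so power is **89.1%**.

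Corrected: the equivalent uncorrected size is (156 − 1/0.15)² / 156 = 142.95. Then z = (0.15 × √142.95 − 1.1575) / 0.5809 = 1.09, so power is **86.3%**. Fisher's exact test gives 86.8%.

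**6. Power after the planned loss.** 353 × 0.87 = 307, or 153 to 154 per group. Power is 88.5-88.7% uncorrected and 85.6-85.8% corrected.

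**7. What could have produced about 156.** These are possibilities only.

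- Loss counted twice: 134 / 0.87 = 154.02, rounded up to 155 per group (310 in total), then inflated again to reach 353. This is close to 312 but not exact.
- Power near 90%: 158 per group (unpooled), 159 (arcsine) or 161 (pooled).
- An intervention rate of 28% at 80% power: 156 per group. This rate was found by solving backwards from 156.

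**The case against.** The strongest objection concerns weight. The discrepancy runs in the safe direction: the trial has more power for its own hypothesis than it claims. Recruitment and follow-up are complete, so no enrolment decision depends on the paragraph, and no estimate, test or type I error rate is affected. All of that stands. It makes this a correction to a stated figure and not a threat to validity.

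A second objection is that a journal article condenses the full protocol, so the formula and the choice of continuity correction may properly be left out. That also stands, and their absence is not part of this point. It does not remove the inconsistency, because no standard variant of the stated inputs gives 156.

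A reader might go further and infer that the stated power or the stated effect must be wrong. The document does not support that. Both may be as intended and 312 may be the error, as the double-allowance route shows. A reader might also conclude that the trial was really sized for 15% versus 28%, since that gives 156 at 80% power. No section mentions 28%, and the Abstract, Introduction and Sample Size Determination all state a doubling. The intended effect is clear; only its link to 312 is not.

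**Conclusion.** The point holds as an inconsistency among stated figures. The required number is 121 per group, or 134 with continuity correction, against 156 stated. Achieved power for 15% versus 30% exceeds the stated 80% by about 6 to 9 percentage points, and by nearly as much after 13% loss. The trial is not underpowered for its stated effect.

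This rests on a comparison of two independent proportions at one time point with equal groups and the full 5% alpha, which is how the article describes the calculation. The mismatch is certain on those terms. Its cause is not: the article leaves open whether the power, the rates or the 312 is the wrong item.

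**What to change.** Retrieve the original calculation and correct Sample Size Determination so that the power, the two rates and the sample size agree. If it shows that loss was already included in 312, say so. If no record survives, keep the hypothesis and state that 156 per group gives about 86-89% power for 15% versus 30% at a two-sided 5% alpha.

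The Introduction needs no change, since its 15% and 30% already match the stated 2-fold increase. The cost is a sentence or two, with no change to enrolment, to the 30% hypothesis or to the analysis. The article says that the analysis is still ongoing, so the correction can be made before results are reported.

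### The final size of 353 is 312 multiplied by 1.13, not divided by 0.87: at 13% loss it leaves about 307 women, 5 short of the stated 312 (minor; power is not threatened)

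*Protocol article*

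**What the plan says.** The Sample Size Determination section of the protocol article lists the planning assumptions as "80% power, 5% 2-sided alpha, and 13% expected loss at follow-up". It takes 15% as the exclusive breastfeeding rate at 6 months and assumes a doubling; the Introduction gives the two rates as 30% and 15%. The Methods part of the abstract says that women were "allocated randomly to an intervention or control group in a 1:1 ratio".

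The section puts the size before loss at 312, or 156 per group, and then states that "the final sample size requirement was 353 participants to allow for 13% loss at follow-up". The Results section calls 353 the target and says it was recruited, and Recruitment, Assignment, and Allocation gives the same number of consenting women. No other loss rate is given, and no other reason for 353.

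**The concern.** Three numbers in one section do not fit together: 312 required, 13% lost, 353 enrolled. A loss at follow-up is a share of the women enrolled. The number to enrol is therefore the number needed at the end divided by the share retained. Adding 13% of the final number gives too few, because the loss is then taken from a larger base than the one used to work out the allowance.

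What is at stake is the accuracy of the stated allowance. A reader who later compares actual retention with the plan would take 13% as the tolerated loss, when the enrolled number tolerates less. This comparison is likely to be made, since Strengths and Limitations expects difficulty in reaching women by telephone.

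**Working it through.** **Inputs.** From Sample Size Determination: 312 before loss (156 per group), 13% loss, 353 final, 80% power, two-sided 5%, control rate 15%. From the Introduction: intervention rate 30%. From the abstract: 1:1 allocation.

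**1. Reproduce the plan's figure.** Multiplying: 312 × (1 + 0.13) = 352.56, rounded up to 353. This is an exact match.

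**2. The allowance that a 13% loss calls for.** N = n / (1 − loss) = 312 / 0.87 = 358.62, so 359.
- Check: 359 × 0.87 = 312.3, which keeps 312; 358 × 0.87 = 311.5, which does not.
- By group: 156 / 0.87 = 179.3, so 180 per group and 360 in total.

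**3. What 353 delivers.**
- Retained at 13% loss: 353 × 0.87 = 307.1, about 307 (153–154 per group).
- Shortfall: 312 − 307 = 5 women at follow-up; 359 − 353 = 6 at enrolment (7 for equal groups).
- Largest loss that still leaves 312: (353 − 312) / 353 = 41 / 353 = 11.6%.

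**4. Effect on power.** Normal approximation for two proportions, pooled variance under the null, unpooled under the alternative. The mean rate is 0.225, so 2 × 0.225 × 0.775 = 0.34875, and 0.15 × 0.85 + 0.30 × 0.70 = 0.3375.

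Power = Φ{[0.15 − 1.960 × √(0.34875/n)] / √(0.3375/n)}. The continuity-corrected version subtracts 1/n from 0.15.

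At n = 153.5 the standard errors are 0.0477 (null) and 0.0469 (alternative), so power = Φ(1.207) = 88.6%.

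| Per group | No correction | Continuity correction |
|---|---|---|
| 156 | 89.1% | 86.3% |
| 153.5 | 88.6% | 85.7% |

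The slip costs about half a percentage point.

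**5. Whether 312 follows from the stated inputs.**
- n = [1.960 × √0.34875 + 0.842 × √0.3375]² / 0.15² = 120.5, so 121 per group, 242 in total.
- With continuity correction: (120.47/4) × [1 + √(1 + 4/(120.47 × 0.15))]² = 133.5, so 134 per group, 268 in total.
- Unpooled variance gives 118 per group and the arcsine method 119.

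None of these gives 156. This is why power at 153–154 per group stays above 80%.

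**The case against.** The strongest reply is that the slip does not matter. It concerns 6 women out of 359 (1.7%) at enrolment, and power stays well above the planned level. Recruitment and follow-up are finished, so the actual loss will replace the planning allowance. All of this stands, and it limits the point to a correction of the reported calculation.

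A second reply is that 13% was meant as an add-on to 312, which would make 353 correct. The wording does not allow this: the section calls the figure "13% expected loss at follow-up", which is a share of those enrolled. Rounding does not explain the gap either.

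A third reply is that 307 misses only a printed number, because the stated rates, power and alpha need 242 to 268. That is true. It also means that the surplus in 312 is unexplained.

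In the other direction, a reader might infer that falling short of 312 leaves the trial underpowered. The document does not support this, since at its own stated rates power at about 307 women is 86% to 89%. Power would fall below 80% only if 312 were exactly the 80% minimum under some assumption that is not printed. In that hypothetical case 307 would give Φ(2.80 × √(307/312) − 1.96) = Φ(0.82), about 79.4%. Nothing in the article states such an assumption.

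**Conclusion.** The point holds as a minor arithmetic error in a stated figure. The allowance was made by multiplication where division was needed, so the printed size does not deliver the printed number of women at the printed loss. The conclusion rests on reading 13% as a share of enrolled women and on taking 312 as the number wanted at follow-up, both of which the section states. The power figures rest also on the stated 15% and 30%, a two-sided 5% test and equal loss in the two groups.

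The larger gap in the same section is that 312 cannot be recovered from the stated inputs. That limits how the correction can be worded, because a power of 88.6% for 153–154 per group cannot stand without explanation next to a stated 80% basis for 156 per group.

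**What to change.** Correct the sentence on loss, with no further enrolment. Possible wording: *353 women enrolled leaves about 307 evaluable (153–154 per group) if 13% are lost; 312 remain evaluable if loss does not exceed about 11.6%.*

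Quote power at 153–154 per group only if two things go with it:
- the method, including whether a continuity correction was used (88.6% without, 85.7% with);
- an account of how 312 was obtained, for example a deliberate margin or an assumption not printed in the article.

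If the origin of 312 cannot be established, say so and leave the power figure out.

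The cost is one sentence, plus a second if the origin of 312 is explained. Design, enrolment and analysis do not change. The stated evaluable number and tolerated loss become slightly less favourable; a power figure, if added, would be higher than the 80% now printed, which is why it needs the explanation beside it.
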